### Safety monitoring and reporting

Ivermectin is well tolerated and has a significant dose safety margin with no safety concerns at much higher doses than clinically required (up to 120 mg in adults, approximately 2000 µg/kg).^40 41^ Over one billion doses have been distributed for control of onchocerciasis and LF with few effects reported beyond minor, reversible events.^42 43^ There have been cases of encephalopathy following ivermectin administration but these have been in the context of loiasis, a disease which has not been detected in Solomon Islands.^44^ Ivermectin is on the WHO Model Essential Medicines List and the Solomon Islands Essential Medicines List for the treatment of scabies.^31 45^ Although topical benzyl benzoate is the standard treatment of scabies in the Solomon Islands, topical 5% permethrin will be used in the study due to its increased efficacy and lower rate of local side effects.^46^ Permethrin is well tolerated with very few side effects, including in infants.^47 48^ Nonetheless, we will record all reported adverse events related to treatment using passive monitoring.

Participants will be advised to report any adverse events to clinic nurses or directly to the study team if the adverse event occurs immediately post MDA. The clinic nurses will relay information to the study coordinator who will document the adverse event and send a report to the Principal Investigator who will, in turn, collate adverse events for reporting to the Data Safety Monitoring Board (DSMB). Any serious adverse events or suspected serious adverse reactions will be reported to the study coordinator by the study team, or clinical staff at the clinics and hospitals in the study area. Hospitals will be briefed on the study and provided with comprehensive reporting forms and the MDA schedule. Hospitals will report any admissions or deaths from study villages for 1 month following administration of the first dose of ivermectin. We will retrospectively review mortality records to ensure all deaths from study villages have been captured. We will review routinely collected summary data on all stillbirths from hospitals in the area for 12 months following MDA.

An independent DSMB will provide oversight to the safety and progress of the trial. The DSMB will meet via teleconference prior to the study, in the first 3 months after MDA and at the conclusion of the study. Any serious adverse events and suspected serious adverse reactions will be reported to the DSMB within 7 days.

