## Methods and analysis

### Study design

The RISE trial is a prospective, open-label comparison of one dose versus two doses of ivermectin-based MDA for the population-level control of scabies (table 1). Using a cluster-randomised design, 20 villages will be randomised to one of two intervention groups in a 1:1 ratio. Randomisation will occur at the village level, rather than the individual level, as the objective is to determine the dosing regimen for controlling scabies within whole communities. Randomisation minimises the possibility of the anticipated difference in the outcome between each group being confounded. A two-dose regimen is an appropriate comparator (rather than no-treatment or placebo) as two-doses of ivermectin-based MDA is the currently accepted dosing regimen. We chose a non-inferiority design because it is unlikely that a one-dose regimen would be superior in effectiveness to a two-dose regimen.

**Table 1 T1:** Key features of the RISE trial

Primary objective	To determine if ivermectin-based MDA with one dose is non-inferior to two-doses in reducing prevalence of scabies at 12 months
Secondary objectives	Impact of one versus two dose ivermectin-based MDA on: Population prevalence of scabies at 24 months Population prevalence of impetigo at 12 and 24 months Number of presentations to health clinics with scabies and impetigo Number of adverse events measured by passive surveillance in the 12-month period following MDA
Design	Prospective, open-label comparison using a cluster-randomised design
Sample size	20 villages (approximately 5000 participants), randomised in a 1:1 ratio to each intervention group
Intervention	Group 1: one dose of ivermectin-based MDA Group 2: two doses of ivermectin-based MDA given 7 to 14 days apart
Study setting	Western Province, Solomon Islands (scabies prevalence approximately 20%)
Inclusion criteria	All residents in the study villages

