### Aims

The primary objective of this study is to determine if ivermectin-based MDA with one dose is non-inferior to two doses in reducing the prevalence of scabies 12 months after the intervention. The secondary objectives are to assess the impact of ivermectin-based MDA on: population prevalence of scabies after 24 months; population prevalence of impetigo after 12 and 24 months; the number of presentations to health clinics with scabies and impetigo before and after the intervention; the number of adverse events measured by passive surveillance in the 12 months after MDA in each study group. The trial will also be measuring outcomes related to the impact of ivermectin MDA on the prevalence and intensity of soil-transmitted helminths; however, this paper focusses on scabies and impetigo outcomes.

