**Figure 2 F2:**
[figure not shown]
Study location in Western Province, Solomon Islands.

Twenty villages will be selected after close consultation with the MHMS. Criteria for selecting the villages include a population of between 180 and 300 people, geographic isolation and willingness to participate in the study. All residents of the 20 selected villages will be eligible to participate. If a resident of a two-dose village does not take the first dose of medication, they will still be eligible to take a dose when the team returns to the village for the second dose.

This is a community-based study, with analysis conducted at the village level, and therefore, all residents are eligible to participate in the follow-up assessment at 12 and 24 months, regardless of whether they received treatment at baseline. Written informed consent will be obtained from all participants. Participants under the age 18 years will require written consent to be provided by a parent or guardian. Consent will be obtained at each study time point (baseline, 12 months and 24 months) (online supplementary file 1).

10.1136/bmjopen-2020-037305.supp1Supplementary data

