#### Secondary outcomes

The analysis for the prevalence of scabies at 24 months and impetigo at 12 and 24 months will be done in the same way as for the primary endpoint.

The change in the number of presentations to health facilities for scabies and impetigo will be analysed in three ways. First, the total number of presentations in the 12 months before MDA will be compared with the number of presentations in months 1 to 12 and 13 to 24 after MDA. Second, we will calculate the proportion of clinic presentations for scabies and impetigo by dividing the number of presentations for scabies and impetigo by the total number of clinic presentations for any condition. We will calculate this proportion for the 12 months before MDA, 1 to 12, and 13 to 24 months after MDA. Calculating the proportion will account for any changes in population size or operational status of health facilities. Third, we will compare the number of clinic presentations for scabies and impetigo in the clinics that service the study villages and compare this with clinic presentation for scabies and impetigo in other clinics in the province, this will be adjusted for population size.

The number of adverse events in each study group will be calculated as a proportion of the total number of participants in each study group that received MDA at baseline. We will also report the number of deaths in the month following MDA in each study group as a proportion of the number of participants in each group.

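### Adverse events: the plan is unclear on whether all or only related events are recorded, and pools by group events that may have had an extra reporting contact in two-dose villages

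*Protocol article*

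**What the plan says.** All references are to the protocol article.

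- **Objective.** Aims lists "the number of adverse events measured by passive surveillance in the 12 months after MDA in each study group" among the secondary objectives, with no condition on cause.
- **Masking.** Study design: "The RISE trial is a prospective, open-label comparison of one dose versus two doses of ivermectin-based MDA for the population-level control of scabies".
- **Contacts.** Table 1 gives the comparator as "Group 2: two doses of ivermectin-based MDA given 7 to 14 days apart". Study setting and participants says of two-dose residents who missed the first dose that "they will still be eligible to take a dose when the team returns to the village for the second dose". No visit to one-dose villages is described between treatment and the 12-month survey.
- **What is recorded.** Safety monitoring and reporting first says "we will record all reported adverse events related to treatment using passive monitoring". Its next paragraph advises participants to "report any adverse events to clinic nurses or directly to the study team if the adverse event occurs immediately post MDA", and has the coordinator document what the nurses pass on. For serious events: "Any serious adverse events or suspected serious adverse reactions will be reported to the study coordinator by the study team". Hospital admissions and deaths in the month after the first dose are reported in both groups.
- **Analysis.** Secondary outcomes: "The number of adverse events in each study group will be calculated as a proportion of the total number of participants" in that group who were treated at baseline. There is no split by dose, onset or reporting route, and no test, margin or decision rule.

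**The concern.** Two features affect how a difference between the groups can be read.

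First, the safety section gives two rules for non-serious events: record those related to treatment, or document whatever participants report. The objective and the analysis simply count adverse events. The published proportion could therefore mean either of two things. No assessor of relatedness is named, and in an open-label trial a judgement made before recording could depend on knowledge of the regimen.

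Second, reporting directly to the study team requires the team to be in the village. In two-dose villages it is there again 7 to 14 days after the first dose, so a resident with an earlier reaction has someone to mention it to. No matching contact is described for one-dose villages.

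The pooled proportion then combines reactions to a real second exposure with any first-dose reactions that come to light only because of the return visit. The contact effect, if present, adds recorded events to the two-dose group and makes one dose look safer. That matters because the Discussion expects a non-inferior one-dose regimen to be attractive for programmes.

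**Working it through.** The document gives no adverse-event rate, reporting rate or safety power, so there is no stated figure to reproduce. The check has two parts.

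**1. The passages side by side (non-serious events)**

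| Place | Which events |
|---|---|
| Aims; Table 1 | adverse events, no relatedness condition |
| Safety monitoring, first paragraph | reported events related to treatment |
| Safety monitoring, second paragraph | any event reported; coordinator documents it |
| Secondary outcomes | adverse events, no relatedness condition |

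The second row is narrower than the other three. Serious events, admissions and deaths are captured whatever the cause, so the inconsistency is confined to non-serious events.

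**2. What an extra contact could do to first-dose events**

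Symbols (all values below are assumptions; none comes from the document):
- r: true risk of a reaction to dose one, equal in both groups
- i: probability that it is reported to the team at the first visit
- c: probability that an event not reported then reaches a clinic nurse
- t: probability that an event missed by both routes is told to the returning team (two-dose villages only)

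Recorded first-dose proportion, treating the routes as independent:
- one-dose: r × [1 − (1−i)(1−c)]
- two-dose: r × [1 − (1−i)(1−c)(1−t)]

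The ratio of the two does not depend on r.

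| Case | i | c | t | One-dose ÷ r | Two-dose ÷ r | Ratio |
|---|---|---|---|---|---|---|
| Late events go only to nurses | any | any | 0 | equal | equal | 1.0 |
| Half reported at once | 50% | 20% | 25% | 1 − 0.5×0.8 = 0.600 | 1 − 0.5×0.8×0.75 = 0.700 | 1.17 |
| Half reported at once | 50% | 5% | 50% | 1 − 0.5×0.95 = 0.525 | 1 − 0.5×0.95×0.5 = 0.7625 | 1.45 |
| None reported at once | 0 | 50% | 10% | 0.50 | 1 − 0.5×0.9 = 0.55 | 1.1 |
| None reported at once | 0 | 30% | 30% | 0.30 | 1 − 0.7×0.7 = 0.51 | 1.7 |
| None reported at once | 0 | 10% | 50% | 0.10 | 1 − 0.9×0.5 = 0.55 | 5.5 |

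With r = 5%, the fifth row gives 1.5% against 2.55% recorded.

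**Why the pooled proportion cannot separate the explanations.** Suppose t = 0, everyone takes both doses, and the second dose carries the same risk and immediate reporting as the first. Events per participant are then exactly twice those of the one-dose group, from exposure alone. Now suppose the second dose causes no reactions at all, with i = 0, c = 20% and t = 25%. The ratio is (1 − 0.8×0.75) ÷ 0.20 = 0.40 ÷ 0.20 = 2.0, from contact alone. The planned analysis would show the same result in both situations.

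**The case against.** The strongest reply is that the plan does not invite late reports to the team. The team route is for events immediately after treatment; later first-dose events are directed to clinic nurses, and that route is the same in both groups. Surveillance is openly passive, and no questioning at the return visit is described. If participants follow the advice, t = 0 and the ratio is 1.0. This stands as far as it goes and is why the contact effect is called possible. But nothing stops the team accepting a late report, and the planned tabulation would not reveal it.

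Four stronger readings are tempting, and the documents do not support them.

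- **Only treatment-related events are recorded, filtered by staff who know the regimen.** One sentence reads that way, but the next paragraph has any reported event documented, and no passage says who filters or when. Leaving the assessor's identity to the full protocol is normal for an article; two conflicting rules are not.
- **The team certainly stays away from one-dose villages for 12 months, or sees nearly everyone at the return visit.** The first is an inference from the schedule described; the second is stated nowhere.
- **The recorded rate would be inflated several-fold, even tenfold.** A ratio of 10.5 arises at i = 0, c = 5%, t = 50% (0.525 ÷ 0.05). It needs every immediate report to the team to be left out, and all its inputs are assumed.
- **All return-visit reports should be removed from the comparison.** Immediate reactions to the second dose are reported at that visit. Removing them would discard real second-dose harm and tilt the comparison towards two doses.

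**Conclusion.** The point holds in limited form. The safety section is inconsistent on whether all reported non-serious events or only related ones are recorded, in an open-label trial. The only team return described before 12 months is to two-dose villages, so first-dose events there may have an extra reporting opportunity. Because the analysis pools all events by group, a higher two-dose proportion could reflect a second exposure, extra contact, or both.

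The size of the contact effect cannot be determined from the document. Under the assumptions tabulated it runs from none (1.0) to a ratio of 5.5, and from 1.17 to 1.45 if half of reactions were reported at once in both groups. Its likely direction favours one dose. The effect of the recording rule could go either way.

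The consequence is confined to a secondary safety comparison that has no decision rule. The primary outcome and the capture of serious events, admissions and deaths are not affected.

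**What to change.** **Safety monitoring and reporting.** Reconcile the two paragraphs so that every reported adverse event is recorded whatever its presumed cause. Judge relatedness afterwards, from a listing that shows neither village nor group.

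**Secondary outcomes.**
- Tabulate events by dose number, onset date and reporting route (team at first visit, team at return visit, clinic nurse, hospital). Count dose number per person, since some two-dose residents take their first dose at the return visit.
- Compare first-dose events between groups over the same onset window, ending before day 7, when no second dose can yet have been given. As a sensitivity analysis, repeat this without first-dose events that began before the return visit and were first reported at it. Show both results: some excluded events would have reached a nurse anyway, so exclusion can overcorrect.
- Keep second-dose events in the overall two-dose total.
- Label the between-group comparison descriptive.

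**Timing and cost.** Trial status says baseline and treatment finished in May to July 2019, so new form fields cannot recover what was not noted. Apply the tabulation to existing records as far as they allow, and report whether unrelated events were in fact recorded and who judged relatedness. No visits or staff are needed. The price is fewer events in the first-dose comparison and some events of unknown route or onset, which should be shown as their own category.

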### Analysis plan

We will account for clustering when calculating all study outcomes by calculating outcomes at the cluster level, and analysing data at the cluster level and not the individual level.^51^ The range of cluster-level outcomes will be reported by group.

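### Hospital listing of admissions and deaths runs from the first dose, so it covers less time after the second dose; the adverse event measure is not a proportion and departs from the cluster-level rule

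*Protocol article*

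**What the plan says.** **Hospital window.** Under Safety monitoring and reporting: "Hospitals will report any admissions or deaths from study villages for 1 month following administration of the first dose of ivermectin". Table 1 (Study design) gives the comparator as "Group 2: two doses of ivermectin-based MDA given 7 to 14 days apart". Under Study setting and participants, residents of two-dose villages who missed the first visit may start late: "they will still be eligible to take a dose when the team returns to the village for the second dose".

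**Other safety capture.** The Aims list as a secondary objective "the number of adverse events measured by passive surveillance in the 12 months after MDA in each study group". Safety monitoring and reporting adds "Any serious adverse events or suspected serious adverse reactions will be reported to the study coordinator by the study team", or by staff at clinics and hospitals, with no end date. For deaths it adds "We will retrospectively review mortality records to ensure all deaths from study villages have been captured". Stillbirth data are reviewed for 12 months.

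**Analysis.** Under Secondary outcomes: "The number of adverse events in each study group will be calculated as a proportion of the total number of participants" in that group who received MDA at baseline. Deaths are reported for the month after MDA, without saying which dose starts the month. The opening of the Analysis plan sets a general rule: "We will account for clustering when calculating all study outcomes by calculating outcomes at the cluster level", with analysis at that level and not at the individual level.

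**The concern.** The two groups differ in the second dose, so the safety question between them is what that dose adds. A hospital listing that starts at the first dose in both groups gives the second dose a shorter follow-up than the single dose receives. Any resulting loss runs one way: it can lower the count of admissions in the two-dose group but not in the one-dose group. The undefined start of the month for deaths adds to this. A reader who counts from the second dose would go past the end of the hospital listing.

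The adverse event measure raises a different problem. Its numerator counts events and its denominator counts people. One person can contribute several events, and two-dose participants have two dosing occasions on which to do so. A higher figure could mean more people affected or more events per person, and the measure cannot tell these apart. It is also defined for the whole study group, although the same Analysis plan says every study outcome is calculated by village. Safety of the two regimens is a stated secondary objective, so the definition matters.

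**Working it through.** The plan gives no figure for the safety comparison, so there is none to reproduce.

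**1. Hospital listing after the last dose**

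Inputs: a one-month window from the first dose (Safety monitoring and reporting) and a dose interval of 7 to 14 days (Table 1). A month of 30 days is assumed.

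Days after second dose = month length − dose interval.

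- Interval of 7 days: 30 − 7 = 23 days (23/30 = 77%).
- Interval of 14 days: 30 − 14 = 16 days (16/30 = 53%).
- One-dose villages: 30 days after the only dose.

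With months of 28 to 31 days the range is 28 − 14 = 14 to 31 − 7 = 24 days. Residents first treated at the second visit get the same short follow-up if the window is set per village. The text does not say whether it is set per village or per person.

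**2. Which month for deaths**

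If the month starts at the first dose, it matches the hospital listing. If it starts at the second dose, it ends 7 + 30 = 37 to 14 + 30 = 44 days after the first. Deaths after day 30 would then rest on the mortality review and serious adverse event reports, not on the hospital listing.

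**3. Adverse event measure against the general rule**

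| | Analysis plan, opening | Secondary outcomes, adverse events |
|---|---|---|
| Level | village | study group |
| Numerator | not stated here | events |
| Denominator | not stated here | people treated at baseline |

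Two participants with one event each and one participant with two events give the same numerator. The ratio is therefore a count of events per person, not the proportion of people affected.

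**4. What clustering would do if an interval were added**

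Inputs: 5260 enrolled (Trial status) and 20 villages, so m = 5260/20 = 263. The document gives no intracluster correlation (ICC) for adverse events; a range of 0.001 to 0.05 is assumed.

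Design effect = 1 + (m − 1) × ICC. A standard error that ignores villages is too small by the square root of this.

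| Assumed ICC | Design effect | Factor on SE |
|---|---|---|
| 0.001 | 1.26 | 1.12 |
| 0.005 | 2.31 | 1.52 |
| 0.01 | 3.62 | 1.90 |
| 0.02 | 6.24 | 2.50 |
| 0.05 | 14.1 | 3.75 |

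As an illustration, assume 2% of participants have an adverse event and 5260/2 = 2630 are treated per group. The 95% half-width for the group difference, ignoring villages, is 1.96 × √(2 × 0.02 × 0.98/2630) = 0.76 percentage points. Multiplying by the factors above gives 1.15 points at an ICC of 0.005, 1.44 at 0.01 and 1.89 at 0.02.

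**The case against.** The strongest reply is that the one-month limit applies to a single source. The stated adverse event outcome has 12 months of passive surveillance in both groups, serious events are reported with no end date, and deaths are checked against mortality records. A reader might infer that 7/30 to 14/30 (23% to 47%) of the month after the second dose goes unobserved. The document does not support that: only the systematic hospital listing ends early. This part of the reply stands in full for adverse events and largely for deaths. It does not cover admissions, because the retrospective review is of mortality records only.

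A reader might also infer that the whole safety comparison is distorted. That is not shown. Both groups have the same calendar window from the first dose, so total observation time is equal, and the second dose falls inside the window. Secondary outcomes names no separate analysis of admissions, and nothing in the document indicates how many late admissions would be missed. What remains is a possible under-capture in one direction, of unknown size.

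On clustering, the article plans no confidence interval, test or margin for adverse events. A claim that the plan's interval is too narrow would therefore criticise an analysis it does not contain, and the size of any such error rests on an assumed ICC. With villages of similar size, the pooled and village-averaged figures would also be close. All of this stands.

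Finally, detail on adverse event tables is commonly left to a statistical analysis plan. That would excuse silence, but this article states a definition, and the definition does not fit the rule that opens the same section.

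**Conclusion.** The point holds in a limited form; it does not touch the primary outcome.

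- **Hospital listing.** It covers about 16 to 23 days after the last dose in two-dose villages against about 30 in one-dose villages, assuming a 30-day month. Late admissions after the second dose can be under-captured in the two-dose group only. The number involved cannot be estimated from the document.
- **Deaths.** The start of the reporting month is undefined and must be reconciled between Safety monitoring and reporting and Secondary outcomes.
- **Adverse event measure.** Events over treated people is not a proportion, and a group-level figure conflicts with the cluster-level rule. This does not depend on any assumed ICC.
- **Precision.** Harm arises only if an interval or test is added without regard to villages. The standard error would then be too small by a factor of about 1.1 to 3.75, for an assumed ICC of 0.001 to 0.05 and 263 people per village.

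**What to change.** **Window.** Use one common period in both groups for hospital admissions and deaths, running to one month after the last scheduled dose. That is 14 + 30 = 44 days from the first visit, applied to one-dose and two-dose villages alike. Anchoring each group to its own last dose would instead give 37 to 44 days of observation against 30. Use the same period for the deaths reported under Secondary outcomes, and say whether it is set per village or per person. Trial status puts baseline MDA in May to July 2019, so the extra days must be taken retrospectively from hospital and mortality records.

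**Adverse events.** Define the outcome as participants with at least one adverse event over participants treated. Calculate it for each village and compare the groups on the village values, as the Analysis plan requires. Give event counts per dose alongside.

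**Cost.** About two more weeks of records to extract, which is possible only if hospital records show village of residence, and revised adverse event tables. No visits are added.
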